### 6.3.1.3 Monitoring, Recording and Reporting of Adverse Events

#### 6.3.1.3.1 General Requirements

During the course of the study, all AEs (including SAEs), irrespective of the relatedness to the study drug, will be recorded on the AE pages of the CRF. During each monitoring visit, the Investigator and the monitor will review all AEs. The Investigator will be

responsible for ensuring that correct information concerning all AEs is included on the appropriate CRF forms.

The following data will be recorded:

- description of the AE: nature, frequency, intensity, time and date of onset and resolution, treatment, outcome, and causal relationship (in the opinion of the Investigator) to the study drug for each AE;
- whether the AE has to be considered as a SAE;
- action taken.

All AEs occurring during the study must be followed-up until the AE has completely resolved, stabilized or the sequelae can be assessed by the Investigator. In case of withdrawal the respective CRF has to be completed.

The results of additional diagnostic measures as the result of an AE, such as laboratory tests, ECG, angiogram, echocardiogram and MRI must be available at site and eventually copied on request.

A flow chart for the reporting of SAEs is shown in Figure 8.

[figure not shown]

**Figure 8: Reporting of Serious Adverse Events**

The Investigator reports all SAEs within 24 h to the Sponsor. The Sponsor will report all serious and unexpected adverse drug reactions (SUSARs) in an expedited fashion to all concerned investigators, Independent Ethics Committees (IECs) and the Competent Authority.

#### 6.3.1.3.2 Reporting of Serious Adverse Events

All SAEs that occur during the period of observation starting with signing of the informed consent and ending with the 6-Month Assessment, and all SAEs occurring up to 30 days after receiving the stem cell injection (study drug) in case of withdrawal, whether considered to be associated with the study drug or not, must be reported by the Investigator. A SAE report must be faxed within 24 hours following knowledge of the event by the Investigator to:

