An obligatory safety follow up is planned for further 18 months after study data closure. Therefore the patients will be required to attend 24 months after the operation Assessment VI. This will be outside the study after data closure. At Assessment VI patient will undergo examination of all safety parameters and will be asked to complete QoL questionnaires. AE documentation and reporting for the safety follow-up will include all (possibly) related AEs and all AEs of specific interest including MACE and death.

The trial will be conducted at seven sites in Germany. Patients will be informed by the study physician and guided additionally through the whole study by a "Study Pass".

A Safety Monitoring Board (SMB) will be responsible for the overall safety of the patients in the trial. See Section 9.9 for further details.

Discontinuation criteria for patients, for parts of the study, and the entire study are described in Section 4.3.

See Appendix 1 for the trial flow chart and Table 2 for the schedule of trial assessments.

In all cases retention of samples of bone marrow and stem cells are stored for safety reasons in the laboratory up to the end of the study. After the end of the study (approx. 2.5 years) the patient may decide what should happen to the stored material: The patient may donate the samples for a research study (pseudonymous) or decide for a further storage or for the destruction of the material. Therefore, all patients will be unblinded at the end of the study and will decide on the use of the material.

During the preparation procedure a small fraction of the cells will be used for research-related investigations (project: “Weitere funktionelle Analysen von adulten Knochenmark-Stammzellen in vitro und in vivo”). The patient agrees to the procedure by a signature on the informed consent form.

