### 4.3 Patient Withdrawal and Replacement

Patients may withdraw from the study at any time without penalty and for any reason without prejudice to his or her future medical care. All patients will be closely monitored by their individual cardiologist and general practitioner and treated as appropriate, according to the guidelines issued by the national and international cardiology organizations that relate to patients with coronary artery disease and patients with congestive heart failure. The Investigators reserve the right to conduct additional follow-up examinations.

Patients must be withdrawn under the following circumstances:

- The patient withdraws consent;
- Pregnancy. If patients are to withdraw due to pregnancy, they should be followed-up until the outcome for the mother and fetus are known.
- If serious clinical events (e.g., emergency surgery, myocardial infarction, stroke, fever  $\geq 38.5^{\circ}\text{C}$ ) occur between recruitment and planned surgery.

Patients may be required to withdraw after discussion with the Sponsor and/or Investigator for the following reasons:

- Adverse event(s);
- At the discretion of the Investigator;
- Violation of eligibility criteria;
- Deviation from the treatment plan specified in the protocol (e.g., incorrect administration of the study drug, failure to attend study visits).

In all cases, the reason(s) for withdrawal, and the primary reason, will be recorded on the case report form (CRF). If a patient is prematurely withdrawn from the study for any reason, the Investigator will make every effort to perform the evaluations described for the Early Termination Visit (see Section 7.2.6.2).

An excessive withdrawal of patients can render the study uninterpretable. Therefore unnecessary withdrawal of patients should be avoided. In case of withdrawal, all efforts should be made to complete and report the observation and justification of withdrawal in as much detail as possible. Withdrawn patients that dropped-out of the study because of SAE will not be replaced. However, patients who are not able to reach the primary endpoint because of their body size/weight may be replaced.

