#### *6.3.1.6 Major Adverse Cardiovascular Events – MACE*

Major adverse cardiovascular events patient alive no/yes, reoperation no/yes, secondary ICU admission no/yes, infarction post-OP no/yes, readmission no/yes, reintervention no/yes, new ventricular arrhythmia no/yes) will be separately assessed at Assessment V (6 months after OP) and 24-Month Follow-Up.

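### In withdrawn patients the routine SAE reporting duty ends at the later of withdrawal and day 30 after the injection, not at month 6, and the protocol does not say whether the month-24 follow-up includes them

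*Protocol*

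**What the plan says.** Section 6.3.1.3.2 sets two SAE reporting periods, whatever the causality. The general one is "starting with signing of the informed consent and ending with the 6-Month Assessment". The second, joined to it by 'and', is "all SAEs occurring up to 30 days after receiving the stem cell injection (study drug) in case of withdrawal". Its 30 days run from the injection on day 0, not from the withdrawal date.

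Other sections that bear on this:

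- **Recording in the study (6.3.1.3.1).** "During the course of the study, all AEs (including SAEs), irrespective of the relatedness to the study drug, will be recorded".
- **Routes to withdrawal (4.3, 5.4).** Section 4.3 has a list headed "Patients may be required to withdraw after discussion with the Sponsor and/or Investigator for the following reasons", and adverse events are its first item. It also foresees drop-out caused by an SAE: "Withdrawn patients that dropped-out of the study because of SAE will not be replaced". Section 5.4 requires withdrawal when an investigator, assessor or patient is unblinded, unless continuation is specifically approved. It names medical emergencies and SAEs among the grounds for breaking the blind.
- **Follow-up to month 24 (3.1, 6.3.1.5, 6.3.1.6).** Section 3.1 states: "An obligatory safety follow up is planned for further 18 months after study data closure". Its scope is possibly related events, events of specific interest, MACE and death. Section 6.3.1.5 has the same general scope. Section 6.3.1.6 says that MACE "will be separately assessed at Assessment V (6 months after OP) and 24-Month Follow-Up".
- **Use of the data (8.1.3, 9.9).** The safety population is everyone randomized. The Safety Monitoring Board is to terminate the trial if class III, IV or V events are significantly more frequent with cells than in the control group (chi-square, p < 0.05).

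**The concern.** The product is injected once, so leaving the study does not end exposure. Yet the same unrelated SAE at month 4 must be reported in a patient who stayed and need not be in a patient withdrawn at month 2. Some routes to withdrawal start with an adverse event, directly or through emergency unblinding, so length of cover can depend on how the patient is doing.

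Both uses of the data count patients by arm: the safety tables on all randomized patients, and the board's comparison, for which no exclusion of withdrawn patients is stated. If withdrawal differs between arms in number, timing or cause, part of any difference in SAE frequency reflects length of observation. The month-24 provisions could close much of the gap, but none of them says whether a withdrawn patient is included.

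**Working it through.** **1. Length of cover.** Inputs: injection on day 0; 30 days (6.3.1.3.2); month 6 ± 2 weeks (Table 2), taken as 182.5 ± 14 = 168.5 to 196.5 days.

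End of routine SAE reporting if withdrawn on day d = max(d, 30).

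| Patient | Reporting ends | Days short of day 182.5 |
|---|---|---|
| Stays | day 182.5 | 0 |
| Withdrawn day 10 | day 30 | 152.5 |
| Withdrawn day 60 | day 60 | 122.5 |
| Withdrawn day 120 | day 120 | 62.5 |

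The shortest cover is 30/182.5 = 16% of the full period. With the visit window it is 30/196.5 = 15% to 30/168.5 = 18%, a gap of 138.5 to 166.5 days. A patient withdrawn after day 30 has no reporting period after withdrawal.

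**2. What the other sections cover after that point.**

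- *Events before withdrawal:* reportable, and followed until resolved, stabilized or loss to follow-up (6.3.1.3.1, 6.3.1.4). An early termination visit is attempted (4.3, 7.2.6.2).
- *Specific-interest events, related events, MACE and deaths:* covered to month 24 if 3.1, 6.3.1.5 and 6.3.1.6 apply to withdrawn patients, which is not stated.
- *Unrelated, non-fatal SAEs that are neither MACE nor in Appendix 2:* no routine duty on any reading.
- *Low cell count (0.1 to below 0.5 × 10⁶):* excluded post hoc but explicitly still followed up (8.1.2). No such statement is made for the surgical complications that lead to post-hoc exclusion in the same section.

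**3. Drop-outs allowed for.** The plan's figure first: difference 4.5, SD 7.5, two-sided 5%. The noncentral t gives power 0.898 at 59 per group and 0.903 at 60, so 60 is right. 60/0.85 = 70.6, hence 71 per group and 142 in all, which agrees with Section 8.7. Drop-outs allowed: 142 − 2 × 60 = 22.

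**4. Possible number of missed events.** The protocol gives no SAE rate, no withdrawal times and no split of the 15%. Assume, as an extreme, that all 22 are injected and withdrawn before day 30. Use the 9.9% six-month MACCE rate cited in Section 1.3, with constant hazard:

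h = −ln(1 − 0.099)/182.5 = 0.000571 per day

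First event between day 30 and day 182.5 = exp(−30h) − exp(−182.5h) = 0.983 − 0.901 = 0.082

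22 × 0.082 = **1.8 patients**, against 142 × 0.099 = 14.1 expected in the whole trial.

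Variations, all assumed:

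| Assumption | Patients |
|---|---|
| 50% of events fall by day 30: 22 × 0.099 × 0.5 | 1.1 |
| 70% of events fall by day 30: 22 × 0.099 × 0.3 | 0.7 |
| Twice the hazard in withdrawn patients | 3.4 |
| Six-month rate 20%, constant hazard | 3.6 |
| Six-month rate 40%, constant hazard | 7.0 |

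The last two rows are there because SAEs of all kinds may be commoner than MACCE. Every row keeps the extreme of 22 early withdrawals.

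**The case against.** The best reply is that the 30-day clause adds cover and removes none. Because 'and' joins the clauses, SAEs up to withdrawal are reportable whenever withdrawal occurs, and a patient withdrawn in the first month is covered a little longer. That is right, and it rules out the reading that reporting stops at day 30 for every withdrawn patient.

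Three other inferences are tempting and not supported:

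- *That the rule hides harm leading to withdrawal.* Such harm precedes withdrawal, so it is reportable and followed, the reason for withdrawal is recorded, and Section 8.6 tabulates adverse events leading to withdrawal.
- *That MACE collection ends at withdrawal.* No section exempts withdrawn patients from Assessment VI. Assessment V doubles as the early termination visit, so the rule in 6.3.1.5 for the time after it can be read to include them. The text leaves this open.
- *That placebo patients have no window because the clause names the stem cell injection.* The clause equates it with study drug, and blinded investigators could not apply it by arm. This is loose wording.

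It is also fair that the 22 are patients allowed for as not evaluable, not early withdrawals. They can include low-cell-count patients who are still followed, patients whose product is not released, and patients without a month-6 MRI. The 9.9% is a MACCE rate, and MACE and death are within the month-24 scope. Nor do the documents show that withdrawn patients are those most likely to have SAEs, since withdrawal also follows from consent, eligibility, deviations and pregnancy.

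What stands is that, after the later of withdrawal and day 30, a class of SAEs is reportable in one patient and not in another, and no section settles whether the remaining follow-up applies.

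**Conclusion.** The concern holds in a limited form. SAE ascertainment is unequal between patients who stay and patients who are withdrawn, and it may depend on outcome because adverse events, SAEs and unblinding are foreseen routes to withdrawal. The inequality is a stated rule, not a detail left to the SAP.

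The loss is probably small: at most about 1 to 2 patients with an event at the cited 9.9% rate, assuming all 22 drop-outs withdrew before day 30 at ordinary risk. It is smaller if Sections 3.1 and 6.3.1.5 cover withdrawn patients, and larger only under the assumed higher rates or hazards above. The direction of any effect on the comparison between arms cannot be told from the protocol. The LVEF endpoint is not touched. This is a cheap improvement, not a change on which the trial's validity depends.

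**What to change.** Reconcile Sections 6.3.1.3.2, 6.3.1.5, 3.1 and 8.1.3 by replacing the withdrawal clause with text such as:

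> For every patient who received study treatment (cells or placebo), SAEs are reported up to month 6 whether or not the patient has been withdrawn. The month-24 safety follow-up, with its present scope, also applies to withdrawn patients. Both end if the patient withdraws consent to further contact.

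The existing 3-month telephone contact and the month-6 and month-24 time points suffice. The month-24 scope should stay as it is: asking for all SAEs at that point would contradict Sections 3.1 and 6.3.1.5.

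Cost: a short amendment, a telephone contact or record check for a small number of withdrawn patients (22 at the very most under the planned drop-out rate), and a few more SAE reports to process.

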**SAE [contact]-hour service)**

**Medical [contact]**

The Investigator should not wait to receive additional information to fully document the event before notifying of a SAE, though additional information may be requested. The minimum information required for an initial report is:

- Sender of report (name, address and phone number of Investigator)
- Date of initial report
- Patient identification (patient number)
- Protocol number
- Investigational medicinal product
- Description of event with outcome, if available, and criteria for seriousness, expectedness and causality

Where applicable, information from relevant laboratory results, hospital case records and autopsy reports should be obtained. The Investigator is also required to submit follow-up reports to Adverse Event Reporting until the SAE has resolved or, in the case of permanent impairment, until the SAE stabilizes. The original SAE form must then be sent by mail to the Clinical Monitor. In addition, the event must be documented in the CRF.

As required, the Sponsor, will report the SAE to the relevant Regulatory Authority and the IECs within the required timeframe, depending on the local regulations. Regulatory agencies will be notified as soon as possible but no later than 7 days after first knowledge of fatal or life-threatening unexpected AR and no later than 15 days after knowledge of the other unexpected SAR.

#### 6.3.1.3.3 Other Procedures for Recording and Reporting Adverse Events

Events with class I and class II severity will be analyzed at the end of the trial period. Events with class III and class IV severity will be reported to the SMB. Details of the SMB are provided in Section 9.9. Class V events must surely be reported to the SMB.

During this study, there will be standard pharmacovigilance monitoring for SARs and SUSARs to allow for annual safety reporting procedures. The Sponsor (or delegate) will be responsible for safety updates to regulatory authorities in accordance with guidelines

and guidance and the German Medicines Act (AMG) and for updating IECs (Independent Ethics Committees) in accordance with the guidelines.

#### *6.3.1.4 Follow-Up of Adverse Events*

All AEs experienced by a patient, irrespective of the suspected causality, will be monitored until the event has resolved, any abnormal laboratory values have returned to baseline or stabilized at a level acceptable to the Investigator and the Clinical Monitor, until there is a satisfactory explanation for the changes observed, or until the patient is lost to follow-up.

After class II to IV AEs, patients will remain hospitalized until complete stabilization. The institutions/physicians following the patients during and after convalescence will be informed about the patient's study participation and advised to increase their level of attention. The study center Investigator will conduct safety-related follow-up examinations on an outpatient basis for a minimum of 6 months or until resolution of these AEs.

#### *6.3.1.5 Adverse Events of Specific Interest*

Events that are listed in Appendix 2 are considered to be of specific interest for the purpose of this study and are monitored in detail. Documentation and reporting of Adverse Events of Specific Interest will be according to the standard procedure of SAE reporting in Section 6.3.1.3.2. continuously up to study end and furthermore as safety follow up to Assessment VI after 24 months. After study termination (Assessment V, 6-Month Follow-Up) AEs not listed as AEs of specific interest will not be documented unless they are possibly, probably or definitely related to the investigational medicinal product or result in death. In case of seriousness all possibly, probably or definitely related AEs will be reported at Assessment VI, 24-Month Follow-Up.

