
Another cell population candidate for the regeneration of ischemic cardiac muscle and vascular endothelium are CD45+ hematopoietic CD34LOW/-/c-kit+, so called side population stem cells with a specific Hoechst 33342 DNA dye efflux pattern (Goodell et al, 1997; Jackson et al, 2001). Orlic et al. (2001) used an alternative method to enrich putative regenerative stem cells for local application by depleting unwanted cell lineages prior to enrichment for the expression of the stem cell factor receptor c-kit from murine bone marrow. Thus concentrated cells, considered to represent hematopoietic stem cells, were observed to incorporate not only into vascular structures but dominantly led to myocardial regeneration (Orlic et al, 2001). Subsequent experiments by this group employed mobilization of stem cells by G-CSF prior to experimental myocardial infarction, which also led to a significant increase in vascular density within the scar, a reduction in mortality, and a significant reduction in infarct size (Orlic et al, 2001).

Although the evidence that angiogenesis occurs in ischemic myocardium is convincing, this new therapeutic option also has a potential for serious side effects (Epstein et al,

2001). Most importantly, bone marrow-derived endothelial cells were found as part of the tumor neo-vasculature in experimental colon cancer (Asahara, 1999). This finding might suggest a risk to trigger the growth of silent tumors by systemic use of pro-angiogenic stem cell therapy.

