**Potential *risks* of cardiac stem cell therapy**

- Transmission of infection
- Tumor formation
- Unwanted tissue formation
- Inflammation
- Immunogenicity
- Ventricular arrhythmia
- Deterioration of heart function

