- Documentation of any AE/SAE and reporting of any SAE that is related to the investigational product (relatedness 3 to 5) since last assessment; documentation of any MACE and any Event of Specific Interest since last assessment (reporting only in case of relatedness 3 to 5); see Section 6.3.1, 6.3.1.5, and 6.3.1.6

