## Appendix 2: Adverse Events of Specific Interest

| Adverse event reporting                                                                         |                          |                          |                                    |                                  |                          |                          |
|-------------------------------------------------------------------------------------------------|--------------------------|--------------------------|------------------------------------|----------------------------------|--------------------------|--------------------------|
|                                                                                                 | 0                        | I                        | II                                 | III                              | IV                       | V                        |
|                                                                                                 | no event                 | asymptomatic             | symptomatic, no specific treatment | symptomatic, treatment necessary | life-threatening         | death                    |
| AV block
 I  II  III |  |  |            |          |  |  |
| Prolonged QT-Interval                                                                           |  |  |            |          |  |  |
| Sinus bradycardia                                                                               |  |  |            |          |  |  |
| Supraventricular arrhythmia                                                                     |  |  |            |          |  |  |

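### The protocol gives differing rules for documenting adverse events between months 6 and 24, and because Appendix 2 omits neoplasms, non-fatal extracardiac tumours judged unrelated need not be recorded

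*Protocol*

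**What the plan says.** The restrictive rule stands in two places. Protocol section 6.3.1.5 says that, once a patient has passed Assessment V, "AEs not listed as AEs of specific interest will not be documented unless they are possibly, probably or definitely related" to the product, or unless they are fatal. Section 3.1 says: "AE documentation and reporting for the safety follow-up will include all (possibly) related AEs and all AEs of specific interest including MACE and death". The list is fixed by 6.3.1.5: "Events that are listed in Appendix 2 are considered to be of specific interest for the purpose of this study".

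Appendix 2 has 12 rows: AV block, prolonged QT, sinus bradycardia, supraventricular arrhythmia, ventricular arrhythmia, vasovagal syncope, left ventricular failure, myocardial ischaemia, cerebral ischaemia, myocarditis, pericardial effusion or pericarditis, and deep sternal wound infection. None covers a tumour or unwanted tissue.

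Section 1.3 lists "Tumor formation" among the potential risks of cardiac stem cell therapy and gives unwanted tissue formation its own line.

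Other places describe Assessment VI more widely. The synopsis lists seven items for that visit, including the recording of AEs with no qualifier and a tumour check by echocardiography. Table 2 marks AEs/SAEs at Assessment VI with no limiting footnote. Section 7.2.6.3 asks for "Documentation of any AE/SAE and reporting of any SAE that is related to the investigational product" (relatedness 3 to 5).

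**The concern.** A follow-up to 24 months can only report what sites were told to write down. The protocol treats tumours as a potential harm. Sections 1.1.2.5 and 1.3 both single out the absence of new ventricular arrhythmia and of neoplasia in earlier work as safety evidence. Ventricular arrhythmia is in Appendix 2; neoplasia is not. From month 6 on, an unlisted event survives only if it is fatal, counts as MACE, or is rated at least possibly related. For a non-fatal tumour outside the heart, documentation as an adverse event then rests on one investigator's causality opinion.

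Two things are at stake. A statement that few or no tumours were seen by month 24 could partly reflect the recording rule. And because the sections differ, sites could apply different rules at the same visit. Neither can be repaired in the analysis, since an event that was never collected cannot be recovered.

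**Working it through.** **Step 1: a test case against each section.** Take a non-fatal tumour outside the heart, arising between months 6 and 24 and rated not related or unlikely.

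| Place in the protocol | What it asks for at Assessment VI | Is the test case recorded? |
|---|---|---|
| 3.1 | Possibly related events, listed events, MACE, deaths | No |
| 6.3.1.5 | Listed events, at least possibly related events, deaths | No |
| Appendix 2 | 12 listed items, none a neoplasm | Not listed |
| Synopsis, safety parameters | Recording of AEs, no limit stated | Yes |
| Table 2 | AEs/SAEs marked, no restricting footnote | Yes |
| 7.2.6.3 | Any AE/SAE, if the relatedness condition governs reporting only | Yes on that reading, otherwise no |
| 6.1.6 and 6.3.2.9 | Echocardiographic check with a yes/no/describe item | No, it concerns the heart |
| 6.3.2.3 | Physical examination findings by body region | Only if visible or palpable |
| 6.3.1.6 | MACE form with a yes/no readmission item | Admission only, without diagnosis |

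The same tumour is required under some sections and excluded under others.

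**Step 2: the same exercise for a tissue change in the heart.** Echocardiography is scheduled at Assessment VI and its form has an item for unwanted tissue changes with no causality filter. The cardiac case is therefore collected outside the adverse event rule. The check is lighter than at earlier visits: Table 2 has no MRI at Assessment VI, and 7.2.6.3 takes the echocardiogram from a practice-based cardiologist.

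**Step 3: reporting as well as documentation.** Section 6.3.1.5 sends events of specific interest through the standard SAE procedure up to Assessment VI. That procedure (6.3.1.3.2) applies whether or not the event is thought to be related. Section 7.2.6.3 reports such events only for relatedness 3 to 5. Adding rows to Appendix 2 would leave this difference in place, so it has to be settled too.

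**Step 4: how many cases could be involved.** The protocol states no tumour rate, so there is no figure to reproduce. As an assumption, take an incidence of 1% to 2% per year. The other inputs are 142 patients (section 8.7) and the interval from month 6 to month 24, which is 18 months or 1.5 years.

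Expected cases = patients × years × annual incidence

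- At 1%: 142 × 1.5 × 0.01 = 2.13
- At 2%: 142 × 1.5 × 0.02 = 4.26
- Per arm (71 patients): 2.13 / 2 = 1.07 to 4.26 / 2 = 2.13
- With the 120 evaluable patients of section 8.7: 120 × 1.5 × 0.01 = 1.8 to 120 × 1.5 × 0.02 = 3.6

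How many of these would go undocumented depends on the share that is extracardiac, non-fatal and rated not related or unlikely. The protocol gives no basis for that share, so the loss could lie anywhere from none to all of them.

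**The case against.** The strongest reply is that the follow-up is not blind to tumours. They are a named safety item at Assessment VI, cardiac tissue changes are recorded whatever the cause, physical examination findings are described by body region, and readmissions are ticked without a causality filter. Deaths are always documented, and the category possible in 6.3.1.2.2 is broad enough to retain many tumours. All of this stands, and it narrows the gap to the test case in Step 1.

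A reader might infer several stronger things that the documents do not support:

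- **That the 24-month follow-up misses the very risk it exists to detect.** Tumours are one of seven items at that visit, and no section makes them its purpose.
- **That 7.2.6.3 flatly contradicts 6.3.1.5.** Its sentence is ambiguous. The relatedness condition may also govern documentation; the bullet then names MACE and events of specific interest separately, which would be redundant if every event were already covered, and it cites 6.3.1.5. Against that, the same bullet attaches a relatedness limit expressly to reporting alone, which favours the wider reading. The wording does not settle it.
- **That the arm comparison is biased.** While causality is judged blind, under-recording should be similar in both arms, so the cost is sensitivity. Section 3.1 provides for unblinding at study end, but its timing relative to Assessment VI is unclear, so differential recording is not established.
- **That section 1.1.2.2 establishes an extracardiac risk for this trial.** The sentence "This finding might suggest a risk to trigger the growth of silent tumors" goes on to limit itself to systemic use, whereas this product is injected locally. The point rests on section 1.3.
- **That most tumours would be judged unrelated and lost.** Nothing in the protocol supports such a share. The assumed incidence may also be too high, since active malignancy is an exclusion criterion (4.2) and full follow-up of all 142 patients is not guaranteed.

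**Conclusion.** The concern holds in a limited form. The rule for months 6 to 24 is not stated consistently, and under its restrictive version a non-fatal extracardiac tumour rated not related or unlikely need not be documented, although section 1.3 names tumour formation as a potential risk. That conclusion comes from the text alone and needs no assumption.

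The consequence is reduced sensitivity of any 24-month tumour statement. In absolute terms it is small: about 2 to 4 tumours in total, or 1 to 2 per arm, if incidence is 1% to 2% per year and all 142 patients are followed for the full 18 months. Such counts are too few for a formal comparison by arm under any recording rule. They also mean that one or two unrecorded cases would noticeably change a descriptive statement. The change is worth making because it is cheap and the lost information cannot be recovered later.

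**What to change.** 1. Add two rows to "Appendix 2: Adverse Events of Specific Interest": new or progressive neoplasm (any site), and unwanted tissue formation. As listed events they would be documented to month 24 regardless of judged causality.
2. State one rule for documenting adverse events between months 6 and 24, and use it in the synopsis, section 3.1, section 6.3.1.5, Table 2 (a footnote at Assessment VI is enough) and section 7.2.6.3.
3. State separately which of the documented events are reported and under what relatedness condition, so that 6.3.1.5 and 7.2.6.3 agree. Reword the bullet in 7.2.6.3 so that it is clear whether the relatedness condition applies to documentation, to reporting, or to both.

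The cost is two lines in the appendix and the case report form, wording changes in five places, and a few more event forms completed at a visit that is already planned.
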